## Methods/Design

### Study design

A two-arm, cluster-randomized controlled trial will be conducted with approximately 40 medical practices, selected from different regions in Germany (Westphalia-Lippe and Schleswig-Holstein). Patients from these medical practices will be assessed on the date of study inclusion (t0) and after 6 (t1) and 12 months (t2). Cluster-randomization is used with medical practices chosen as the unit of allocation because it is most practical in this setting and minimizes the risk of spillover effects from the intervention to the control group [7]. Moreover, the collaboration between physicians, their medical assistants and AOK will be assessed via qualitative interviews conducted 12 months after study begin. Finally, the intervention’s cost-effectiveness will be assessed.

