### Evaluation

#### Outcome evaluation

Primary and secondary outcomes are assessed on the individual participant level 12 months after the initial consultation with the physician. The primary outcome is the amount of cigarettes smoked per day (30-day prevalence), measured via the quantity-frequency index [19]. Secondary outcomes are the rate of abstinence from smoking, quality of life measured via sum scores calculated from the SF-12 [23], and respiratory complaints measured via sum scores calculated from the Visual Simplified Respiratory Questionnaire [25].

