### Statistical methods

#### Data analysis

The main research questions will be evaluated via mixed models, which make it possible to examine effects and their interactions on different levels (physicians and patients). According to the intent-to-treat principle, all randomized patients will be included in the primary analyses. In the analysis of abstinence rates, patients lost to follow-up will be assumed to have returned to smoking [27, 28]. Table 2 provides a summary of the hypotheses along with comparison groups, statistical method and the outcomes of interest. Other than the 6-month follow-up conducted with patients via telephone, no interim analyses are planned.

**Table 2 Tab2:** Hypotheses

Hypotheses	Comparison	Statistical method	Outcome measure
Primary hypothesis			
Smoke reduction	CG-IG	Mixed models	Quantity-frequency index
Secondary hypotheses			
Rate of abstinence	CG-IG	Chi-square	Abstinence
Health-related quality of life	CG-IG	Mixed models	SF-12
Respiratory complaints	CG-IG	Mixed models	Visual Simplified Respiratory Questionnaire
Process evaluation hypotheses			
Referral	CG-IG	Descriptive	Amount of patients referred to the smoking cessation program via referral form
Uptake	CG-IG	Descriptive	Amount of patients attending the smoking cessation program
Cost-effectiveness and cost-utility	CG-IG	ICER	Quantity-frequency index, QALY

The telephone interviews conducted with physicians and AOK staff will be recorded digitally, transcribed and analyzed via qualitative content analysis [26]. The health economic analysis will be performed by calculating the incremental cost-effectiveness ratio (ICER) for the 12-month follow-up, based on routine cost data provided by AOK. As measures of effects, the quantity frequency index, as well as QALYs, will be employed. For this purpose, differences in the mean costs ($$ \overline{\boldsymbol{C}} $$) and mean effects (***Ē***) between intervention and control group will be related to one another:$$ ICER=\frac{{\overline{C}}_{IG}-{\overline{C}}_{CG}}{{\overline{E}}_{IG}-{\overline{E}}_{CG}}=\frac{\varDelta \overline{C}}{\varDelta \overline{E}} $$

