### Sample size calculation

According to a survey of 11,000 physicians, on average, 53 patients are treated in medical practices per day [29]. Approximately 15 of these patients are health insured by AOK, which holds one third of the nationwide market share. According to epidemiological data, approximately 7 % of patients smoke 20 or more cigarettes per day. Assuming a participation rate of 50 %, physicians should be able to recruit around 10 patients for participation in the study per month. A meta-analysis by Stead and colleagues [7] demonstrates that among at-risk patients, the relative risk of being abstinent from smoking at follow-up is 1.65 for participants of intensive interventions, compared to participants of minimal interventions (with around 12 and 7 % cessation rates in the intervention and control groups, respectively). This value was transformed into a standardized mean difference (Cohen’s d) due to the metric scaling of our primary outcome. The expected small to moderate effect of Cohen’s d = 0.30 requires that data from 352 persons are available for sufficiently powered (β = 0.20) independent samples t-tests (α = 0.05). Accounting for the effect of clustering (intraclass correlation coefficient of 0.05) [30, 31]suggests that data from 34 medical practices with an average cluster size of 20 should be analyzed (340 patients per group, 680 in total). An estimated 15 % drop-out rate for medical practices means that 40 medical practices should be recruited. Due to an estimated 15 % of patients lost to follow-up, a total of 800 patients will be recruited for participation in the study. Assuming a 20 % participation rate in the smoking cessation program, 68 patients from the intervention group are expected to participate in the smoking cessation program. Figure 1 illustrates the expected flow of medical practices and patients through the study.

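### Table 2 tests abstinence with a chi-square test that ignores randomisation by practice; at the protocol's own ICC of 0.05 the two-sided type I error is about 16%, not 5%

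*Protocol article*

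**What the plan says.** All references are to the protocol article.

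- **Study design** fixes the unit of randomisation: "Cluster-randomization is used with medical practices chosen as the unit of allocation".
- **Outcome evaluation** fixes the level of measurement: "Primary and secondary outcomes are assessed on the individual participant level 12 months after the initial consultation with the physician".
- **Data analysis** gives the general rule: "The main research questions will be evaluated via mixed models". The reason offered is that such models handle the physician level and the patient level together.
- **Table 2** then assigns a method to each hypothesis. The quantity-frequency index, the SF-12 and the respiratory questionnaire get mixed models. The abstinence row reads "Rate of abstinence CG-IG Chi-square Abstinence".
- **Sample size calculation** treats clustering as material: "Accounting for the effect of clustering (intraclass correlation coefficient of 0.05", with the result that "data from 34 medical practices with an average cluster size of 20 should be analyzed (340 patients per group, 680 in total".

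The only other reference to clustering in an analysis is in the health economic part, where net-benefit regression is to account for it. Nothing comparable is said about abstinence.

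**The concern.** Patients of one practice share a physician, a medical assistant and a local programme offer, so their outcomes tend to be alike. A chi-square test on the pooled 2 × 2 table takes its variance from independent patients and leaves out the variation between practices. In a trial randomised by practice, that variation is part of the error against which the arms must be compared. The p-value is therefore too small, and any confidence interval built on the same variance is too narrow.

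Abstinence is listed first among the secondary hypotheses, and the planned effect size was itself converted from cessation rates of about 12% and 7%. The Discussion says the results should inform funding and policy. Chance differences between a few dozen practices could thus be reported as a demonstrated effect on quitting.

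**Working it through.** **Inputs**

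- Practices analysed: 34, so 17 per arm at 1:1; average cluster size m = 20; 340 patients per arm (Sample size calculation).
- ICC ρ = 0.05 (same section). It is the only ICC in the document and was used for the metric primary outcome.
- α = 0.05 and power 0.80. Sidedness is not stated.
- Abstinence rates of about 12% and 7% (same section).
- Patients lost to follow-up are counted as smoking (Data analysis), so they stay in the denominator and m stays near 20 for this outcome.

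**Step 1: reproduce the plan's own figure**

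The plan states that d = 0.30 "requires that data from 352 persons are available for sufficiently powered (β = 0.20) independent samples t-tests (α = 0.05". A two-sided two-sample t-test with d = 0.30 needs 175.4, rounded up to 176 per arm, which is 352 in total. The figure therefore reproduces with a two-sided α.

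Design effect: DE = 1 + (m − 1)ρ = 1 + 19 × 0.05 = 1.95.

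352 × 1.95 = 686, or 34.3 practices of 20. The plan has 34 practices and 680 patients, so it used this design effect to within rounding. Then 34/0.85 = 40 practices and 680/0.85 = 800 patients, as stated.

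**Step 2: true type I error of the unadjusted test**

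The true variance of the difference in proportions is DE times the variance the chi-square test assumes. The standard error is understated by √1.95 = 1.396, and the true two-sided error is

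2 × [1 − Φ(1.96/√DE)] = 2 × [1 − Φ(1.404)] = 0.160.

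A nominal 95% interval on the same variance would cover about 84%.

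**Step 3: check by simulation**

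Beta-binomial data under the null, 17 practices of 20 per arm, 100,000 trials per setting, ρ = 0.05: the uncorrected chi-square test rejects in 15.9% to 16.0% of trials for abstinence rates of 7% to 12%. With the Yates correction it rejects in about 13% to 14%.

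**Step 4: dependence on the ICC (m = 20, no continuity correction)**

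| ICC | Design effect | True two-sided error |
|---|---|---|
| 0.01 | 1.19 | 7.2% |
| 0.02 | 1.38 | 9.5% |
| 0.03 | 1.57 | 11.8% |
| 0.05 | 1.95 | 16.0% |
| 0.10 | 2.90 | 25.0% |

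**Step 5: what a valid test leaves**

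To hold 5% at DE = 1.95, the chi-square statistic would have to exceed 3.84 × 1.95 = 7.49. The effective size per arm is 340/1.95 = 174. Power for 12% against 7% is then about 36%, compared with a nominal 60% if 340 patients per arm are counted as independent.

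**The case against.** Five points can be made in the plan's defence.

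- **The 16% is conditional.** It borrows an ICC meant for cigarettes per day and applies it to a binary outcome with a rate of about 7% to 12%. This stands: the document gives no ICC for abstinence, so 16% is the value at the plan's own assumption, not a known error rate. A smaller ICC shrinks the inflation but does not remove it. Only a continuity-corrected test at an ICC of 0.01 comes close to nominal, at about 5.3% to 5.6% in the simulation with 17 practices of 20 per arm.
- **The cell does not say unadjusted.** Cluster-adjusted chi-square tests exist, and Table 2 is a summary in a condensed article. But the adjacent rows name multilevel methods and this one names a test whose standard form has no cluster term. If an adjusted version is intended, the entry must say so.
- **The general rule may cover only the primary question.** Then table and text do not conflict. Yet the section on aims counts abstinence among its main hypotheses. Even on the narrow reading, the other two secondary outcomes still receive mixed models, so secondary status does not explain the exception.
- **No confidence interval for abstinence is announced.** True; the coverage figure applies only if one is computed from the same variance.
- **Abstinence is secondary.** Also true: the primary comparison uses a mixed model, and the sample size allows for clustering. That limits the damage to this hypothesis but does not make its test valid.

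**Conclusion.** The concern holds. The method stated for abstinence does not fit a trial randomised by practice. It departs from how the protocol treats its other tested patient outcomes and from its own sample size assumption. This is a wrong method named in the document, not a detail left for later.

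At an ICC of 0.05 and 20 patients per practice, the two-sided type I error is about 16%, roughly three times nominal. The figure rests on carrying the sample-size ICC over to abstinence, on clusters of equal size and on an uncorrected test. With an ICC of 0.01 to 0.02 the error is about 7% to 9.5%; with the Yates correction at 0.05 it is about 13% to 14%. The conclusion for the primary outcome is unaffected.

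**What to change.** In the abstinence row of Table 2, replace the chi-square entry with a method that accounts for practices. A suitable choice is a mixed-effects logistic regression with practice as random intercept, arm and region (the stratification factor) as fixed effects, and a small-sample correction suited to 34 to 40 practices. GEE with a small-sample sandwich variance, or a practice-level comparison, would serve equally well. Add one sentence saying that the odds ratio or risk difference will be reported with a cluster-adjusted confidence interval. The essential element is the adjustment for practice; the remaining details can be settled in the analysis plan, provided this is done before the data are analysed.

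The cost is one table cell and one sentence, with no new data and no change to the primary analysis. The interval becomes wider. The sponsor should also expect power of only about 36% for 12% against 7% at an ICC of 0.05, so a non-significant abstinence result should not be read as evidence of no effect.

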### Study aim and hypotheses

The aim of the present study is to evaluate the effectiveness and cost-effectiveness of CSCI with respect to tobacco consumption, health status and health care costs, compared to usual care. The main hypotheses are listed.

The primary hypothesis is as follows:

Patients in the intervention group smoke fewer cigarettes per day (30-day prevalence) compared to patients in the control group.

The secondary hypotheses are as follows:Patients in the intervention group are abstinent from smoking more often compared to patients in the control group.Patients in the intervention group have higher health-related quality of life compared to patients in the control group.Patients in the intervention group have fewer respiratory complaints, compared to patients in the control group.

The hypotheses related to the process evaluation are as follows:The amount of patients referred to the smoking cessation program is greater in the intervention group compared to the control group.The amount of patients who attend the smoking cessation program is greater in the intervention group compared to the control group.Cost-effectiveness (cost per reduced quantity-frequency index) and cost-utility (cost per quality-adjusted life year; QALY) are greater in the intervention group compared to the control group.

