### Measures and evaluation

#### Measures

Patients are handed a questionnaire (t0) at the medical practice containing the quantity-frequency index [19], the Fagerström Test for Nicotine Dependence (FTND) [20], SmoCess-GP [21], Questionnaire to assess readiness to change among smokers (FÄR) [22], the Short Form SF-12 [23], the EQ-5D-3L [24] and the Visual Simplified Respiratory Questionnaire (VSRQ) [25]. Physicians specify the patient’s smoking status and the diagnosis for the severity of the cardiovascular disease or COPD on a documentation sheet. Follow-up takes place after 6 (t1) and 12 (t2) months via telephone by a research assistant from the University Medical Center Hamburg-Eppendorf. Moreover, qualitative interviews will be conducted with physicians assigned to the intervention group, their medical assistants and the AOK smoking cessation program instructors after 12 months in order to determine the network’s quality. The measures used in this study are validated and have been used previously in similar studies. All measures are listed in Table 1 along with the time of measurement and person being assessed.

**Table 1 Tab1:** Measurement process and time

Time of measurement	Person	Constructs
Screening	Patient	Smoking status (>20 cigarettes per day yes/no) and/or presence of cardiovascular disease or COPD
Questionnaire (t0)	Patient	Smoking status:
		Fagerström Test for Nicotine Dependence (FTND) [20]
		Quantity-frequency index (30 days): Amount of days on which patients smoked during the last 30 days, average amount of cigarettes consumed per day [19]
		SmoCess-Questionnaire to assess primary care for smoking cessation [21]
		Health status:
		Health-related quality of life SF-12 [23]
		EQ-5D-3L [24]
		Respiratory complaints: Visual Simplified Respiratory Questionnaire (VSRQ) [25]
		Motivation:
		Questionnaire to assess readiness to change among smokers (FÄR) [22]
Documentation sheet (t0)	Physician	Smoking history (number of years of smoking), relevant clinical indications (severity of cardiovascular disease or COPD)
Questionnaire (t1)	Patient	Smoking status:
		Fagerström Test for Nicotine Dependence (FTND) [20]
		Quantity-frequency index (30 days): Amount of days on which patients smoked during the last 30 days, average amount of cigarettes consumed per day [19]
		SmoCess-Questionnaire to assess primary care for smoking cessation [21]
		Health status:
		Health-related quality of life SF-12 [23]
		EQ-5D-3L [24]

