### Collaborative smoking cessation intervention (CSCI)

Physicians in the CSCI group will receive a brochure containing detailed information about the intervention, the steps involved in delivering it to patients and the required materials. The steps involved in delivering the intervention are as follows: During a personal consultation physicians motivate patients to participate in the smoking cessation program. Patients who wish to participate in the program are handed a flyer containing detailed information about the date, time and place of the program and are instructed to contact the nearest AOK branch office to register for the program. Patients who fail to do so within 14 days are sent a written reminder by AOK. Physicians issue a referral form for each patient willing to participate in the program and send it to AOK. Physicians receive a one-time payment of €25.50 from AOK for every patient referred to the smoking cessation program via referral form. During subsequent consultations, physicians ask patients about their participation in the program. Physicians assigned to the control group will provide usual care (defined as the care provided by physicians under routine conditions, when not trained to deliver the CSCI).

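### The between-arm referral hypothesis is measured by counting a form that the protocol describes only as a step of the intervention, so the contrast does not measure a difference in referral behaviour

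*Protocol article*

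**What the plan says.** Under Study aim and hypotheses, the first process-evaluation hypothesis is directional and between arms: "The amount of patients referred to the smoking cessation program is greater in the intervention group compared to the control group". Table 2, under Data analysis, sets the comparison as control versus intervention group, the method as descriptive, and the outcome as "Amount of patients referred to the smoking cessation program via referral form".

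The form itself is introduced in the section on the CSCI. That section opens with the brochure given to CSCI physicians and then lists the steps, introduced by "The steps involved in delivering the intervention are as follows". One of them is: "Physicians issue a referral form for each patient willing to participate in the program and send it to AOK". The payment follows: "Physicians receive a one-time payment of €25.50 from AOK for every patient referred to the smoking cessation program via referral form". Only after this does the section turn to the control group, whose physicians give usual care, defined as routine care without training in the CSCI. It mentions no form for them.

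Two other planned sources bear on the same question. Table 2 has a separate uptake row that counts attendance in both groups. Table 1 lists the "SmoCess-Questionnaire to assess primary care for smoking cessation" among the patient questionnaires at baseline, 6 months and 12 months.

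**The concern.** A between-arm outcome has to be something that either arm could produce. Here the outcome is a document that, as far as the article says, belongs to one arm's treatment. A control physician who recommends the insurer's program in conversation has made a referral in any ordinary sense, but the measure would not record it.

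Such recommendations are plausible. The Background reports that German guidelines recommend cessation advice from physicians to every patient, that certified programs are reimbursed, and that this program is the one German health insurers most often offer.

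What is at stake is the interpretation of the process evaluation. The Abstract names motivating patients and referring them as the physician's part of the intervention. A large contrast in form counts would look like evidence that this step rose above usual care, when it might reflect only who was given the form. The planned interviews would not correct this, because on the practice side they cover intervention-group physicians and their assistants only.

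**Working it through.** **Where the form appears.** It occurs in two places: the referral row of Table 2, and the CSCI section, as a delivery step and as the trigger for payment. No section gives control practices a form or another way of recording a referral. A control count at or near zero is therefore an inference from the text, not a statement in it.

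**What satisfies the hypothesis.** Take the control count as 0. The hypothesis that the intervention count is greater is then met by a single form. With n patients and a form-referral rate p (assumed, since the article gives none), and ignoring clustering:

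P(at least one form) = 1 − (1 − p)^n

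The Sample size calculation gives 340 analysed patients per group. Form counts need no patient follow-up, so the recruited number, 800 / 2 = 400 per group, is shown as well.

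| Assumed p | n = 340 | n = 400 |
|---|---|---|
| 0.5 % | 82 % | 87 % |
| 1 % | 97 % | 98 % |
| 5 % | over 99.99 % | over 99.99 % |

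**What the count shows when there is no true difference.** Suppose both arms refer the same share q of patients by any route, and only intervention physicians use the form. The expected counts among 340 per group are 340 × q against 0:

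- q = 5 %: 340 × 0.05 = 17 against 0
- q = 10 %: 340 × 0.10 = 34 against 0

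The true difference in referral is nil in both cases. The rates are assumptions chosen to show the mechanism, and the article offers no figure for referral in either arm.

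**The plan's nearest figure.** The Sample size calculation expects 68 intervention-group patients in the program, and 0.20 × 340 = 68 reproduces it. This is a count of participants, not of forms. Patients register themselves with an AOK branch, so attendance does not fix the number of forms.

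**What else depends on the form.** The primary outcome is the quantity-frequency index. The secondary outcomes are abstinence, the SF-12 and the respiratory questionnaire. Uptake is attendance, and the effect measures in the economic analysis are the quantity-frequency index and QALYs. None of these is measured by the form. The payment per recommendation enters the intervention's costing, where it is a real cost and properly counted.

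**The case against.** The strongest reply is that nothing in the article says control practices lack the form or that AOK would refuse one from them. The sentences on issuing the form and on payment say only physicians, without naming a group, and this is a condensed article. That stands as far as it goes. A reader might infer that the control count is zero by design, and the documents do not establish that. But both sentences belong to the account of delivering the intervention and come before the control group is introduced. As described, control physicians have no route to a form.

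A second reply is that the trial still collects relevant information in both arms: attendance is compared separately, and SmoCess is given to every patient. This also stands. It rules out the stronger reading that the trial cannot learn whether referral rose above usual care. Attendance is only a partial substitute, however. It lies downstream of referral and also reflects other influences, such as the written reminder AOK sends after 14 days. SmoCess item content is not shown, so whether it records referral to the program cannot be judged here.

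Third, the row is descriptive, with no test and no decision rule. That limits the consequence but does not repair the measure. A descriptive contrast will still be read against a stated directional hypothesis.

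Two further readings go too far. One is that the hypothesis cannot fail: it fails if the intervention arm issues no forms, or no more than the control arm. The other is that the plan implies 68 forms against none, since 68 is the expected number of participants.

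**Conclusion.** The point holds in limited form. The outcome chosen in Table 2 does not fit the hypothesis it is meant to address. It counts use of an intervention component, so almost any form use in the intervention arm confirms the hypothesis, and the contrast says little about how often physicians in either arm refer. This is a measure the protocol names and fixes badly, not a detail left for another document.

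The conclusion rests on one inference, that control practices generate few or no forms, and on the possibility that some control physicians recommend the program without one. The reach is one descriptive process outcome. The trial's conclusions on smoking, quality of life, respiratory complaints, attendance and cost-effectiveness do not turn on it. It should be corrected, but it does not threaten the main results.

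**What to change.** Report the referral-form count for the intervention arm only, as a measure of delivery and fidelity.

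Base any between-arm comparison of referral on a measure obtained identically in both arms. The natural candidate is patient-reported physician recommendation or referral from SmoCess at 6 and 12 months, if its items cover this. Present it next to the attendance comparison already planned. If no common measure is available, drop the between-arm referral hypothesis and keep uptake as the between-arm process comparison. If control practices do in fact have the form, the text should say so and state how their referrals are recorded.

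If SmoCess has a suitable item, the change is confined to the Table 2 row and the matching hypothesis. The price is that patient recall replaces an administrative count. If it has none, adding an item would alter a questionnaire already in use: recruitment started in June 2014, and three ethics committees have approved the study. In that case, dropping the between-arm hypothesis is the cheaper course.
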